#### Recruitment

Participants are recruited from participating DEPs associated with three institutions across Ontario. A clinician at each site identifies potential eligible participants during their regularly scheduled clinical appointment. Interested individuals meet with a site coordinator who provides them with an information brochure and a consent form to review. Interested participants contact the research assistant using the dedicated study phone line. The research assistant obtains and documents verbal informed consent and collects baseline outcome measures (refer to Fig. 2, Part A). Participants are then randomized to one of the study arms. Following randomization, the site coordinator collects clinical information (refer to Fig. 2, Part B) and provides participants in the ITG with a study-specific mobile phone. Participants enter initial clinical information into the application (medications, etc.) while in clinic and the data is reviewed for accuracy by a clinician (nurse, nurse practitioner, or certified diabetes educator). Participants in the WLC group receive their application-enabled phone in person following completion of the control phase (three months after enrollment).

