#### Allocation

Randomization is centralized, web-based and generated by the Applied Health Research Centre (AHRC) at the Li Ka Shing Knowledge Institute of St. Michael’s Hospital. Randomization is stratified by site using randomly permuted blocks of varying sizes, which are not known by the study team.

Once the participant has been enrolled and the baseline assessments are completed, randomization occurs in REDCap™, a web-based electronic data entry system, where the participant is automatically assigned a group allocation (ITG or WLC).

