#### Data collection

Baseline information including demographics and health status will be collected using an electronic case report form (CRF) (refer to Fig. 2). HbA1c values will be recorded at baseline, 3 months, and 6 months. Participants who do not have a recent value within two weeks of the study assessment will be given a requisition to perform blood work during the first study visit. Baseline information will be collected by a research assistant via a telephone call, after which the participant will be formally enrolled in the study. Participants who fail to complete the baseline assessment will not be enrolled. Follow up data will be collected using a secure online questionnaire administered via REDCap™ that can be completed by participants from any device with an internet browser and connection (computer, tablet etc.). Weekly reminders will be sent to participants who fail to complete the questionnaire, with a maximum of three reminders. Participants who express a preference for phone communication will be contacted by the research assistant, following the same reminder protocol. Application utilization data is tracked directly through the application and will be extracted at the end of the study.

Healthcare utilization and cost outcome measures will be obtained from health administrative data available through the Institute for Clinical Evaluative Sciences (ICES). At the time of study enrolment, patients will be asked to provide consent to link their OHIP number to health administrative data. ICES is a non-profit research institute with a secure and expansive repository of Ontario’s health-related administrative data from hospital, physician, long term care and other related health services paid for by the provincial health insurance plan. These data are linked using encrypted identifiers. Data from this study will be linked to ICES data using encrypted health card identifiers created by ICES authorized personnel. ICES is a prescribed entity and data custodian under the Personal Health Information Protection Act (PHIPPA).

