#### Data analysis

All data will be analyzed according to an intention to treat principle. Patient characteristics and baseline HbA1c levels will be summarized using descriptive statistics, including means, quartiles and standard deviations for continuous variables and proportions for categorical variables. The primary outcome, HbA1c levels between treatment groups, will be analyzed using an analysis of covariance (ANCOVA) with follow-up at three months. PROMs and PREMs will be analyzed using an ANCOVA evaluated at 3 months as well. Continuous secondary outcomes including emergency department visits, physician visits, and hypoglycemic episodes will be analyzed using Poisson regression predicted with the two treatment groups. Ordinal categorical variables including medication adherence and frequency of glucose monitoring will be analyzed using an ordinal regression model for the two treatment groups. We will use regression analyses to separately estimate the difference in healthcare costs between the intervention and control groups and include any covariates that are observed to be different between groups in baseline comparisons. To identify the regression model that fits best with the cost data and potential skew, we will follow the steps suggested by Manning and Mullahy [30] to decide between regression on transformed cost data or generalized linear models.

Six-month follow-up data for the immediate treatment group will be analyzed descriptively. In addition, HbA1c levels will be compared at the 6-month point between the two treatment groups using an ANCOVA which will control for baseline HbA1c levels. Application utilization data will be analyzed descriptively, including time (mean duration of use), general frequency of use (mean uses per week), and frequency of use for each application feature. Subgroup analyses based on site and patient demographics, including age, sex, ethnicity, education, and income [31], will also be conducted. All statistical analyses will be performed using R version 3.0.3 (The R Foundation for Statistical Computing; Vienna, Austria).

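### The count and ordinal secondary models name neither site nor the outcome's baseline value, so they give up some power on those outcomes

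*Protocol article*

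**What the plan says.** The Data analysis section of the protocol article sets out its models one outcome type at a time. Hypoglycaemic episodes and visits to physicians and emergency departments get "Poisson regression predicted with the two treatment groups". For adherence to medication and how often glucose is monitored, the sentence is: "Ordinal categorical variables including medication adherence and frequency of glucose monitoring will be analyzed using an ordinal regression model for the two treatment groups". No further term is named in either.

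Elsewhere the same section does mention adjustment. The 6-month HbA1c comparison controls for baseline HbA1c. The cost regressions will "include any covariates that are observed to be different between groups in baseline comparisons". HbA1c at 3 months and the patient-reported measures are analysed by ANCOVA.

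Three other statements bear on what could be adjusted for:

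- Allocation: "Randomization is stratified by site using randomly permuted blocks of varying sizes".
- Recruitment: before randomisation the research assistant "collects baseline outcome measures (refer to Fig. 2, Part A"). Data collection adds: "Participants who fail to complete the baseline assessment will not be enrolled".
- Data collection and Table 1: with consent, participants are linked to provincial administrative data, whose sources include outpatient physician visits and emergency department visits.

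**The concern.** Visit rates, adherence and monitoring habits plausibly persist within a patient, so the earlier value should help to predict the 3-month value. A model with arm as its only term leaves that variation in the comparison and lowers the chance of detecting a true difference. It also ignores the factor on which randomisation was stratified.

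These outcomes bear on the secondary objectives, and the article states no power for any of them. An inconclusive result could therefore reflect an inefficient model as much as the absence of an effect.

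**Working it through.** **1. The plan's own figure.** Inputs from the Power calculation section: difference 0.7, SD 2, correlation 0.80, alpha 0.05, 300 × 0.85 = 255 analysed. Equal arms (127.5 each) and a two-sided test are assumed.

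- Residual SD = 2 × √(1 − 0.80²) = 1.2.
- SE = 1.2 × √(2/127.5) = 0.150.
- Power = Φ(0.7/0.150 − 1.96) = Φ(2.70) = 0.9965, which agrees with the stated 0.997.
- Without the baseline covariate, SE = 2 × √(2/127.5) = 0.250 and power = Φ(2.79 − 1.96) = 0.798.

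This shows what a baseline value is worth in the primary analysis. It rests on r = 0.80 for HbA1c and does not carry over to the other outcomes.

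**2. Count and ordinal outcomes.** The article gives no event rates, category distributions or baseline correlations for these, so every input below is an assumption. Each model was simulated with 255 patients, with and without the baseline value.

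- *Ordinal*: 5-level proportional-odds model, 300 runs per setting. r is the correlation of a continuous baseline score with the latent outcome. A baseline category would carry less information than this score.
- *Count*: Poisson regression with robust SEs, 1,000 runs per setting. Control mean 3, log rate ratio −0.25. Patients differ by a log-normal person effect with the SD shown. r is the correlation of that effect between baseline and follow-up. The covariate is log(baseline count + 0.5).

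| Model | Assumed setting | Power, arm only | Power, arm + baseline | Gain (points) |
|---|---|---|---|---|
| Ordinal | r 0.3, log OR 0.6 | 0.700 | 0.770 | 7 |
| Ordinal | r 0.5, log OR 0.6 | 0.607 | 0.757 | 15 |
| Ordinal | r 0.7, log OR 0.8 | 0.680 | 0.950 | 27 |
| Count | SD 0.6, r 0.5 | 0.619 | 0.651 | 3 |
| Count | SD 0.6, r 0.8 | 0.605 | 0.688 | 8 |
| Count | SD 0.6, r 1.0 | 0.610 | 0.749 | 14 |
| Count | SD 1.0, r 0.5 | 0.316 | 0.337 | 2 |
| Count | SD 1.0, r 0.8 | 0.329 | 0.434 | 11 |
| Count | SD 1.0, r 1.0 | 0.305 | 0.689 | 38 |

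Monte Carlo error on a single power is about √(0.7 × 0.3/300) = 0.026 for the ordinal rows and √(0.62 × 0.38/1000) = 0.015 for the count rows. Both models were fitted to the same simulated data sets. No site effect was simulated, so the contribution of site is not sized.

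**3. Where the ordinal gain comes from.** It does not come from a smaller SE. The SE of the log odds ratio rose from 0.225 to 0.228, 0.231 and 0.240 across the three settings. The estimate moved away from zero: 0.558 to 0.608, 0.504 to 0.612, and 0.545 to 0.807. In the last setting the ratio of estimate to SE goes from 0.545/0.225 = 2.4 to 0.807/0.240 = 3.4. The odds ratio is non-collapsible, so the adjusted model estimates a different, conditional effect.

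**4. Overdispersion is a separate matter.** In the arm-only Poisson model the model-based SE averaged 0.077 to 0.078. The actual SD of the estimate was 0.114 to 0.118 with person-effect SD 0.6, and 0.174 to 0.181 with SD 1.0. That is why the table uses robust SEs.

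**The case against.** The strongest reply is that a condensed article commonly leaves covariate lists to the analysis plan. The ordinal sentence names a comparison; it does not say that nothing else enters. Even the 3-month HbA1c ANCOVA is described without naming its covariate, although the power calculation plainly relies on baseline HbA1c. This has real weight for the ordinal models. It has less for the Poisson models, where the wording states what the model is predicted with, in a section that spells out adjustment for costs and 6-month HbA1c.

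Second, Fig. 2 is not shown, so it cannot be confirmed that each of these outcomes is recorded at baseline. Part B of the form is completed after randomisation. For visits, the article describes linkage but no look-back before enrolment, and does not say whether the modelled counts come from the linked data or from the questionnaire. This stands, and it limits the remedy to baseline values that exist.

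Third, the familiar rule that adjustment multiplies the variance by 1 − r² (0.91, 0.75 and 0.64 at r = 0.3, 0.5 and 0.6) is a linear-model result and should not be turned into patient numbers for count or ordinal models. This stands too.

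Finally, a reader might infer that chance baseline differences bias the arm-only estimates. They do not: such differences are part of ordinary sampling error, which a correctly specified SE already covers.

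**Conclusion.** The point holds as one of efficiency on secondary outcomes. As described, the count and ordinal models name treatment group and nothing else, although site is a stratification factor and baseline or pre-enrolment information is at least partly available. The comparison is valid under randomisation and the primary analysis is unaffected.

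The loss cannot be fixed from the documents. Under the assumed inputs it runs from about 2 to 3 power points (counts, r = 0.5) to about 27 (ordinal, r = 0.7) and 38 (counts with strong overdispersion whose person effect is fully shared with baseline). The top of the range needs favourable assumptions.

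Two stronger readings are tempting and are not supported. One is that the plan rules out adjustment: the text never says so, and the ordinal sentence in particular leaves it open. The other is that precision is discarded throughout: for the ordinal models the SE does not shrink with adjustment, and the gain is in power for a conditional effect.

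**What to change.** State in the analysis plan, before outcome data are examined, that the count and ordinal models include:

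- site, as the stratification factor;
- the baseline value of the same outcome where it is collected before allocation;
- for visits, a count over a fixed period before enrolment from the linked administrative data, suitably transformed (for example, the log of the count plus a small constant).

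Fix these covariates in advance and do not select them by observed imbalance. Report the ordinal odds ratio as a conditional effect. Say separately how overdispersion of the counts will be handled, because baseline adjustment does not by itself resolve it.

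The cost is a change of analysis wording, a little more analysis work and a look-back in data already due to be linked. With 14 participants recruited when the article was written, the change is easy to make early.

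If the full analysis plan already contains these terms, no change is needed beyond aligning the article's description with it.

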**Fig. 3 Fig3:**
[figure not shown]
Modified Mobile Application Rating Scale

In this study, costs of healthcare utilization are used to measure resource intensity. Table 1 outlines the databases used to assess these costs, which will be used to determine frequency and intensity of healthcare utilization and overall individual costs using methods developed for use with Ontario data [29]. Costs of health care resource use will be quantified for patients with algorithms developed for patient-level costing using health administrative data and implemented at ICES [29]. Costs for each encounter that generated an encounter-specific payment (e.g., prescriptions, fee-for-service physician visits) are measured as the fee paid for the service. Costs for hospital encounters are determined using the appropriate resource intensity weight for that particular care setting and the weighted cost derived based on Ontario spending. Costs for long-term care are measured as a fixed per diem based on prevailing government payment rates. Emergency department physicians receive substantial alternative payments that are not visit-related, and the algorithms also ascribe those payments, generally on an average per-patient approach. Capitation payments are calculated based on the payment rate and the particular model of primary care for each patient’s physician in each month of the study period. Team-based payments for family health teams and physician bonus payments for pay-for-performance are not ascribed to individual patients and thus are not included in the analysis.

**Table 1 Tab1:** Databases and cost components used in the calculation of health system costs before, during, and after cancer treatment

Database	Description	Cost component
Ontario Health Insurance Plan and (OHIP)	Contains claims paid by OHIP for services provided by all eligible health care providers, including physicians, groups, and laboratories.	• Outpatient physician visits • Laboratory services • Non-physician services
National Ambulatory Care and Reporting System	Contains data from hospital- and community-based ambulatory care services, including day surgery, outpatient clinics, and emergency departments.	• Emergency department visits • Dialysis visits • Oncology clinic visits

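### The cost regressions choose covariates by observed baseline imbalance, which selects on chance rather than prognosis and gives up precision; prespecify the set instead

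*Protocol article*

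**What the plan says.** In the protocol article's Data analysis section (the one before the power calculation), the cost analysis is set out as follows: "We will use regression analyses to separately estimate the difference in healthcare costs between the intervention and control groups". The same sentence says the models will "include any covariates that are observed to be different between groups in baseline comparisons". No candidate list, test or threshold is given, and prognostic strength plays no part. No other section names a covariate for cost.

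The form of the cost model is also left to the data, but by a cited published procedure used to "decide between regression on transformed cost data or generalized linear models". For HbA1c at 6 months, by contrast, the section fixes the covariate in advance, "using an ANCOVA which will control for baseline HbA1c levels".

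Under Allocation, randomisation is central and web-based, in permuted blocks stratified by site. Under Data collection, cost comes from linked administrative records: "ICES is a non-profit research institute with a secure and expansive repository of Ontario’s health-related administrative data", and at enrolment "patients will be asked to provide consent to link their OHIP number to health administrative data". No pre-enrolment cost period is mentioned.

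**The concern.** Under concealed random allocation, a baseline difference between arms says nothing about whether the variable predicts cost. A rule that admits variables because they differ will often admit irrelevant ones and will usually leave out the important ones, because important variables are as likely to be balanced as any others. Site shows this most clearly. Stratified blocks are there to balance it, so under this rule the stratification factor is unlikely ever to enter the model.

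The criterion is also undefined. *Different* could mean a p-value, a standardised difference or a judgement by eye, so two analysts could reach different covariate sets from the same data.

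Health system cost is a stated secondary objective, and the Discussion section says the results will inform cost-effectiveness and scale-up. The section itself expects skewed costs, and the wait-list arm crosses over after three months. Precision on this outcome is therefore worth keeping.

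**Working it through.** **The plan's own figure.** There is no power or variance figure for cost. The only power figure is for the primary outcome: difference 0.7, SD 2, baseline to follow-up correlation 0.80, 255 evaluable (300 × 0.85), two-sided alpha 0.05 and 1:1 allocation assumed. The residual SD is 2 × √(1 − 0.80²) = 1.2. With 127.5 per arm, power is 0.9965, which agrees with the stated 0.997. Without the baseline covariate it would be 0.798. For HbA1c, then, the plan relies on a prognostic covariate fixed in advance; for cost it does not.

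**How often chance triggers the rule.** Assume that *different* means p < 0.05 and that the k baseline variables are independent. Neither the threshold nor k is in the document.

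P(at least one) = 1 − 0.95^k

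- k = 10: 0.401
- k = 15: 0.537
- k = 20: 0.642

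Any single variable, however prognostic, enters in about 1 trial in 20.

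**What prespecifying prior cost would gain over no adjustment.** In a linear model the variance of the treatment difference is multiplied by 1 − r², where r is the correlation of prior with follow-up cost (assumed).

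- r = 0.3: 1 − 0.09 = 0.91, a 9% cut; 1/0.91 = 1.10
- r = 0.5: 1 − 0.25 = 0.75, a 25% cut; 1/0.75 = 1.33
- r = 0.6: 1 − 0.36 = 0.64, a 36% cut; 1/0.64 = 1.56

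The inverses give the equivalent sample size: 10% to 56% more patients over r = 0.3 to 0.6.

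**What the rule itself does.** A simulation used 255 participants, ten independent baseline covariates (one of them prior cost), a normal outcome standing for log cost, no treatment effect, selection at p < 0.05 and 6000 runs per setting. Columns 2 to 4 give the empirical SD of the estimated difference, in outcome SD units.

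| r | Unadjusted | Imbalance rule | Prior cost prespecified | Mean reported SE, rule | Type I error, rule |
|---|---|---|---|---|---|
| 0.3 | 0.1270 | 0.1259 | 0.1212 | 0.1255 | 0.053 |
| 0.5 | 0.1259 | 0.1216 | 0.1087 | 0.1250 | 0.040 |
| 0.7 | 0.1250 | 0.1154 | 0.0885 | 0.1239 | 0.038 |

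The Monte Carlo standard error of the type I error is about √(0.05 × 0.95/6000) = 0.003. The first value is therefore nominal and the other two are below nominal.

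The variance reduction from prespecification, measured against the rule rather than against no adjustment, is:

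- r = 0.3: 1 − (0.1212/0.1259)² = 7%
- r = 0.5: 1 − (0.1087/0.1216)² = 20%
- r = 0.7: 1 − (0.0885/0.1154)² = 41%

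The rule recovers a little precision because it corrects the worst imbalances. The reported standard error hardly reflects this (0.1239 reported against 0.1154 actual at r = 0.7), so the intervals are slightly too wide.

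**The case against.** A reader might infer that selecting covariates from the data makes the confidence intervals invalid and inflates false positives. That does not follow. The rule looks at baseline variables, not at cost, and applied mechanically it gave type I error at or below 5% in every setting simulated. Inflation would require the choice to be made with the cost results in view. The undefined criterion does not prevent that, but nothing in the document says it will happen.

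A reader might also say that the plan ignores a strong predictor already held at ICES. The document supports less than this. The rule would admit prior cost if it happened to differ, and the text does not bar other covariates. That prior cost predicts follow-up cost is an assumption. That it can be extracted is inferred from the description of the repository and the linkage consent; no look-back period is stated. Table 1 adds that the drug benefit database mainly covers people aged 65 and over, so prior drug cost may be incomplete for younger participants.

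The figures are also open to challenge. The number of variables, the threshold, the correlation and the length of the cost window are not in the document. The 1 − r² formula is for a linear model, while the plan may end with a generalised linear model. Skew is already addressed by the cited model-selection procedure. All of this stands, and it limits the size claimed. It does not rescue the rule: this is stated text, not detail left to an analysis plan, and imbalance remains the wrong criterion in a randomised comparison.

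**Conclusion.** The point holds as one about efficiency and prespecification. The rule selects covariates by chance imbalance, leaves its criterion undefined, and prespecifies neither the stratification factor nor a likely strong predictor. The consequence is lost precision and somewhat conservative intervals for a secondary outcome.

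The size is illustrative. Chance triggers the rule in 40% to 64% of trials, given 10 to 20 independent variables and a 5% threshold. The variance forgone is 9% to 36% against no adjustment, given a correlation of 0.3 to 0.6 and a linear model, and slightly less against the rule as written. Neither invalid intervals nor deliberate neglect of available prior cost data is shown. The primary HbA1c comparison and its power do not depend on this text.

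**What to change.** Delete the imbalance rule. Before any cost data are analysed, name one covariate set for the cost regressions and use it whatever the observed balance:

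- site, as the stratification factor;
- pre-enrolment ICES cost over a fixed look-back window, for linked participants, once it is confirmed that the linkage consent covers that period, with a note that drug cost may be incomplete under age 65;
- age, sex and baseline HbA1c as reasonable additions, which are a matter of choice rather than a consequence of the criticism.

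The cited procedure for choosing the model form can stay. The cost is a change of wording and one further data extraction; no extra patient contact is needed. The article's Trial status section reports 14 participants recruited out of a target of 300, so at that stage the change was early and cheap.
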